### Awareness of assignment

Before starting the study, collaboration agreements will be signed with the institutions interested in receiving the designed intervention. Subsequently, after identifying the study sites, their consent to participate in the study will be obtained.

Once the schools, courses, and students who will participate in the study have been defined, the school principals, teachers, and students will be contacted to explain the objectives of the intervention, the way it will be performed, and the measurements that will be taken. Since the evaluation instruments will be answered online, the students will be contacted by telephone or WhatsApp to ensure both their participation and follow-up. The final follow-up of the cohort is tentatively scheduled for August 2024.

Since the GRTs is a mixed experimental design, the next phase will evaluate the implementation of the program, in order to analyze how the implementation of a comprehensive, preventive program of sexual health facilitates or impedes a gender-transformative intervention. For this we will conduct semi-structured interviews with those persons who will perform the intervention (teachers, psychologists or guidance counselors) and focus groups of students who participate in the intervention.

These techniques will allow collating and triangulating the results and exploring the particulars of each case, which will complement the findings of the GRTs. The interviews and focus groups will approach the relations between different dimensions of the implementation process and the results experienced by the participants from the gender-transforming approach (benefits for adolescent females, males, and LGTB students, changes in gender norms and stereotypes, among others).

Finally, since this is a mixed study, the information from the experimental phase and implementation will be integrated. This implies analyzing the qualitative results of the trial and then determining how the qualitative results empower the trial [23]. Thus the results obtained from the GRTs may be explained using the information from the experiences of the participants about the implementation process of the program.

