### Participants: eligibility criteria

The intervention will be directed exclusively to students of the 10^th^ and 11^th^ grades who are enrolled in one of the education establishments that depend on the Municipality of Santiago. The inclusion criteria for these schools will be the following: (i) have students of these grades enrolled; (ii) not being an education center oriented to adults or persons deprived of liberty (e.g., closed or semi-closed compounds of Gendarmería de Chile or the National Service for Minors); (iii) have regularity in teaching and learning (for example, schools that were not partially interrupted in 2022 by student manifestations); and (iv) have informed consent of the director. The inclusion criteria for the students will be (i) having 90% or greater attendance in classes: (ii) providing informed consent of voluntary participation; and (iii) having explicit and informed consent of their parents or guardians.

The selected students will be randomly divided into the study and control groups; the intervention will take place in the same schools that the students attend. The assignment to groups will use simple random sampling, performed in two stages. In the first stage, the available schools will be randomly assigned to the study and control groups, while the second stage will randomly select the groups in each school that will participate. The study groups will receive a 10-session intervention in sexual education, covering topics related to preventive sexual conduct, gender equity, and mental health. The control groups will not receive intervention; they will continue with the sexual orientation that each school provides to its students. Sexual orientation is general and is provided by the Ministry of Education. The goal is to evaluate and diagnose the behaviors and reproductive health needs of adolescents, addressing the values adopted regarding the decision to engage in sexual relationships and/or have multiple sexual partners, as well as perceptions of risk.

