### Randomization

The assignment of the participants to the groups will be implemented in a two-stage selection of the students; since there are already existing teaching-learning processes in process in the schools, with their time limitations, we will have to choose entire “courses” (in Chilean secondary schools, a course is a group of about 40 students who have all classes together) rather than choose individual students.

We will establish groups among the schools to compensate for their different sizes; some schools in the commune are much larger than others (four or more courses per grade. Thus, we will divide the schools into two blocks: one with the largest schools and one with the medium- and small-sized schools. In the second stage, courses that meet the inclusion criteria to participate in the study will be selected randomly within each block. Table 1 details the distribution of the samples.

**Table 1 Tab1:** Samples to be selected

	**Study group** **No. of students per grade**		**Control group** **No. of students per grade**		
**School**	*10th grade*	*11th grade*	*10th grade*	*11th grade*	Total
*1*	---	---	31	28	59
*2*	---	---	33	27	60
*3*	---	---	34	34	68
*4*	---	---	26	30	56
*5*	---	---	33	32	65
*6*	29	27	---	---	56
*7*	29	30	---	---	59
*8*	28	29	---	---	57
*9*	25	31	---	---	56
*10*	*40*	*33*	---	---	73
	151	150	157	151	
**Sample totals**	**301**		**308**		**609**

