### Allocation process

The allocation sequence will be generated using random numbers produced by the statistical program R. A single investigator will carry out both the sequence of participants’ assignments and their assignment to each group ([name]).

To ensure a blind analysis, the professional in charge of data analysis ([name]) will not know to which group the participants belong. Therefore, the database will be anonymized by assigning codes, which will only be known by another team professional ([name]). Unmasking is not considered to be permitted under any circumstances.

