### Outcomes

Before implementing the workshop, we will perform a base-level measurement of the variables in the students. Later we will measure the result variables in two moments, just after the workshop closes and 3 months after the closure, in order to evaluate the results obtained by the intervention, to determine the effect of the program.

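### Schools are randomised before students are approached and before the baseline visit, so consent and at least part of the baseline can be influenced by knowledge of the arm

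*Protocol article*

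**What the plan says.** The order of assignment is set out under *Participants: eligibility criteria*: "In the first stage, the available schools will be randomly assigned to the study and control groups, while the second stage will randomly select the". What this later step selects is the classes taking part within each school. The *Randomization* section confirms that intact classes are taken, not individual students.

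Under *Awareness of assignment*: "Once the schools, courses, and students who will participate in the study have been defined, the school principals, teachers, and students will be contacted". The purpose of that contact is "to explain the objectives of the intervention, the way it will be performed, and the measurements that will be taken".

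Individual agreement is an inclusion criterion. The student must consent, and so must the family: "having explicit and informed consent of their parents or guardians".

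Under *Outcomes*, baseline is tied to the start of the programme and not to allocation: "Before implementing the workshop, we will perform a base-level measurement of the variables in the students".

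Table 2 marks informed consent, assent and allocation in the same column, −t1. The column labelled baseline is t1. The knowledge test and ad hoc survey are first marked at t1. The sexism, trans-attitude and modern homophobia scales and the PSC-17 are marked at both −t1 and t1.

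Under *Allocation process*: "A single investigator will carry out both the sequence of participants’ assignments and their assignment to each group". Blinding is described for the data analyst only.

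**The concern.** When whole schools are randomised but individuals must still agree to take part, randomisation balances the schools and not the people who later consent. If families or recruiters can know the arm when consent is sought, the two samples can differ for reasons connected with the outcome.

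That connection is plausible here. The protocol's own Background describes the regional culture as conservative and treats gender norms and attitudes as determinants of adolescent sexual health. A family opposed to gender-focused sexual education has a reason to decline in a study school. It has less reason to decline in a control school, where teaching continues as before. The outcomes include sexism, homophobia and attitudes toward trans persons, so refusal could depend on arm and outcome together.

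The second route is the baseline itself. Every outcome is defined as a change and measured by self-report. A student who already knows that the school will run the programme may answer the baseline differently, and that answer then enters the effect estimate directly.

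**Working it through.** The point concerns the order of events. No figure in the protocol is in dispute, so the check is to put the statements in sequence.

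1. **School assignment comes before course selection.** The eligibility section calls these the first and second stages.
2. **Contact comes after course selection.** *Awareness of assignment* has principals, teachers and students contacted once schools, courses and students have been defined.
3. **From 1 and 2, contact comes after school assignment.** Courses cannot be defined until the second stage, which follows the first.
4. **Consent cannot come before contact.** Student and parental consent are inclusion criteria, so the analysed sample is settled after the school's arm is set. This is an inference, because the section speaks of schools and courses being defined, not allocated. It is the most natural reading of the two sections together.
5. **Baseline against allocation.** Table 2 gives:

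| Item | −t1 | t1 |
|---|---|---|
| Consent, assent | x | |
| Allocation | x | |
| Knowledge test, ad hoc survey | | x |
| Three attitude scales, PSC-17 | x | x |

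For the knowledge test and ad hoc survey, the first measurement falls at a time point after the one holding allocation. For the attitude scales and PSC-17, a measurement before allocation is possible but not stated, and the table does not say which of the two marks is the baseline used for change.

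6. **Is the arm recognisable?** Control schools receive no programme. In study schools, the school's own psychosocial staff are trained and deliver ten weekly sessions. The programme is explained at contact. No masking of recruiters, families or students is described.

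7. **Does analysing change remove the problem?** Take the effect as the between-arm difference in (follow-up − baseline).
 - A stable difference *b* between arms, present at both times, contributes *b* − *b* = 0, so it largely cancels.
 - If knowledge of the arm shifts baseline answers in study schools by *s* and the shift is absent at follow-up, the contribution is 0 − *s* = −*s*. It does not cancel.
 - If the students who consent in one arm would have changed over time differently anyway by *t*, the contribution is *t*. It does not cancel.

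The document gives no value for *s*, for *t* or for refusal by arm.

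**The case against.** The strongest reply is that the order is not fully fixed. Consent, assent and allocation share one column of Table 2, with consent listed first. The eligibility section also speaks of selected students being randomly divided, which could suggest that students come first. The attitude scales and PSC-17 have a −t1 mark. The flow chart is not shown and consent pages were removed, so an arm-neutral information sheet cannot be excluded. This is also a condensed article. These points stand to the extent that consent after allocation is a well-supported inference and not an explicit statement, and that a pre-allocation measurement of the attitude scales and PSC-17 remains possible. They do not reverse the reading: the two-stage description and the contact sentence give an order, and nothing in the text promises consent or baseline before the arm is disclosed.

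Three stronger readings are tempting and are not supported.

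- **That all baseline attitudes are certainly answered with the arm known.** The −t1 marks prevent that conclusion.
- **That one investigator both generating and assigning shows the allocation reaches recruiters.** The *Allocation process* section does not say that this person recruits or obtains consent.
- **That the bias can be sized.** A reader might assume 10–20% excess refusal in study schools and decliners who differ by 0.3–0.5 SD. That gives 0.1 × 0.3 = 0.03 to 0.2 × 0.5 = 0.10 SD, or 15–50% of 0.2 SD. Both inputs are assumptions without support in the document. The protocol's 0.2 is in points with no SD given. A stable difference of this kind is also the sort that would largely cancel in change scores.

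The reply on cost has some force too: facilitators are school staff who must be trained, and schools have limited time.

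**Conclusion.** The concern holds as a risk built into the planned order. Followed as written, the plan most likely obtains individual consent after the school's arm is set. It takes the baseline knowledge test and ad hoc survey at a time point after allocation, and it leaves open when the attitude scales and PSC-17 are first answered relative to allocation. With a recognisable arm and no described masking of recruiters, families or students, consent and self-reported baseline can be influenced by the arm. Baseline adjustment or change scores may remove part of this but cannot be relied on to remove it.

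The conclusion rests on reading the two-stage assignment and the contact sentence as one sequence, and on the absence of any statement that the arm is withheld. The direction and size of any bias cannot be derived from the document. The change is worth making because it is simple and closes both routes; the trial is not shown to be biased.

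**What to change.** Change the order and state it explicitly:

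1. Obtain school agreement and select courses in all ten schools.
2. Obtain student and parental consent in all of them with one arm-neutral information sheet.
3. Complete the baseline questionnaire in all schools.
4. Only then release the school allocation.

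In Table 2, move the allocation row to after baseline. Resolve the double marks at −t1 and t1 for the attitude scales and PSC-17, stating which measurement is the baseline. Report consent rates by arm.

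The cost is a re-sequencing of planned steps, one table correction, and less lead time for training facilitators in the study schools. This cost is real, because the programme has to fit ten weekly sessions into school schedules.

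If the allocation has already been released, the order cannot be recovered. In that case, state the actual order of consent, baseline and disclosure, report consent rates and baseline scores by arm, and name recruitment bias as a limitation.

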### Intervention: description of Focus-on

Focus-on is a comprehensive program of sexual education for adolescents. Its design follows the guidelines of the Intervention Mapping Approach [26] and the orientations proposed by the Framework for Gender-Transformative Health Promotion [16]. Specifically considered are (i) the theories, contents, and strategies of the randomized controlled trial of comprehensive interventions for adolescents performed in the last 10 years [27]; and (ii) the results of a previous study in the object population on the implementation of an intervention in sexual health education. Both studies were done by the team that created the program.

The program is based on three fundamental theories as transverse axes: the Theory of Planned Behavior [28], the Framework for Gender-Transformative Health Promotion [16], and the Ecological Focus of Human Development [29]. Some sessions will use the precepts of the Theory of Social Learning [30], the Cognitive-Behavioral Theory using the emotion-regulating model of Gross [31], and the Transtheoretical Change Model [32].

The intervention has a participative focus, thus the activities are designed to promote processes of knowledge, understanding, application, analysis, and reflection in the adolescents. The activities aim to improve the capacity for critical thinking, favor the retention and communication of the new information, increase the motivation to listen and learn actively, and to improve interpersonal abilities. The execution of the intervention uses three pillars: (i) preventive sexual behavior; (ii) gender equity; and (iii) mental health. These pillars approach their different objectives -promote preventive sexual behavior, gender equity in sexual health, and improve aspects of mental health related to sexuality.

The intervention consists of ten weekly sessions, each lasting 1 h, which (except the first, which is an introduction to the program) treat these pillars gradually, from the basic to the most advanced aspects. The teams that will perform the intervention will be composed of at least two professionals of the psychosocial area (mainly psychologists, social workers, and/or guidance counselors) of the schools included in the study, who will be capacitated in the correct implementation of Focus-on.

Based on the nature of this trial, no relevant concomitant care is required. There is also no specific treatment allowed or prohibited during the trial. Similarly, no particular retention strategy is foreseen, and no special criteria exist for interrupting or modifying the assigned interventions.

### Outcomes

Before implementing the workshop, we will perform a base-level measurement of the variables in the students. Later we will measure the result variables in two moments, just after the workshop closes and 3 months after the closure, in order to evaluate the results obtained by the intervention, to determine the effect of the program.

The result variables of the intervention will be the following: (a) change in knowledge of sexuality manage correctly information on topics related to the biological components of sexuality such as reproduction, prevention of STI and pregnancy, among others; (b) change in preventive sexual behavior, which may be related to (i) behavior or intention to prevent STI and pregnancy, or (ii) sexual abstinence or intention to postpone initiation of sexual life; (c) change in gender attitude related to (i) positive disposition towards persons of different genders and sexual orientation, and (ii) empowering in sexuality of LGBT and female students; (d) change in components of mental health related to sexual health, decrease of internalizing-externalizing symptomology, and improvement in self-efficacy (Table 2). The following instruments will be used:*Knowledge test* [33]. This is a 34-item multiple choice instrument which was designed to evaluate the effectiveness of interventions in sexual education to improve knowledge on sexuality in adolescents; it evaluates areas including pregnancy, STI, physical development, and others. Its reliability is *α* = 0.89.*Ad hoc survey*. It was elaborated by the research team to evaluate the behavior and intention of preventive behavior in sexuality, self-efficacy. and empowerment in sexuality in LGTB and female students. Ad-hoc surveys have been used and reported in other randomized controlled trial of interventions in sexual health (e.g.. Coyle [34], Goesling [35]. and Yakubu [36]). This survey will follow the guidelines developed by Manaseri [37] and Jirapongsuwan [38].*Scale for detection of sexism in adolescents (DSA)* [39]. This is an instrument of 26 items developed for adolescents. It evaluates sexism (attitude of superiority towards women), differentiating between hostile and benevolent sexism. The response scale for the items is a Likert type with six alternatives (from 1 = disagree completely to 6 = agree completely). Its reliability is *α* = 0.881.*Scale of negative attitudes toward trans persons (NATP)* [40]. It measures attitude as an expression of prejudice towards trans persons. It has nine items with a Likert scale with five response options, from 1 = disagree completely to 5 = agree completely. Its reliability is *α* = 0.886.*Short version of modern homophobia scale* [41]. It measures homophobic attitudes in the dimensions of personal discomfort, institutional, and deviation/changeability. It is composed of 46 items that evaluate attitudes towards lesbians and gays on a Likert scale of 1–5. Its reliability is *α* = 0.80.*Pediatric symptom checklist (PSC-17)* [42]. This is an abbreviated version of the 35-item PSC [43]. It evaluates general psychosocial functioning, detecting emotional and behavioral difficulties in children and adolescents [44]. Its reliability is *α* = 0.72. PSC-17 is self-administered by adolescents, evaluating the existence of internalizing difficulties (e.g., despair and sadness), externalizing difficulties (e.g., difficulties in social relations such as disobedience of norms and fights with others), and attention difficulties (e.g., difficulty in concentration -60,66-). As in other studies (e.g., Penner [45]), this instrument will be used to evaluate the adolescents’ mental health. The baseline and follow-up evaluations will be obtained confidentially, and be recorded in files managed by the team responsible for the study.

**Table 2 Tab2:** Enrollment, intervention, and assessments

	**Instruments**		**Baseline**	**Post**	**3 months**
**Timepoint**		−*t*_1_	*t*_1_	*t*_2_	*t*_3_

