### Objectives of the study

The main objective of this study is to evaluate the effectiveness of a preventive-comprehensive program of sexual education in schools directed to students, using a mixed experimental design [23].

Given that comprehensive programs of sexual health have more effective results in attitudes and knowledge, and that a program that incorporates a gender-transformative perspective contributes to equity in sexual health, we hypothesize that the intervention designed and implemented in the experimental group: (i) will increase their sexuality knowledge level; (ii) will increase their preventive sexual behavior (or intentions); (iii) will favor a gender-positive attitude; and (iv) will decrease internalizing and externalizing problems and attention in mental health. The secondary objective is to examine the implementation intervention process, that is, identify the strengths and obstacles in the real context in which the study intervention is performed, to understand the determinants and strategies of the success of the implementation.

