### Sample size

There are currently 6518 students enrolled in the 10^th^ and 11^th^ grades in State-financed schools in the commune of Santiago. Using a 99% confidence level and a 5% error margin, the sample framework is 605 students, which will be divided into the study and control groups. The statistical power is determined using an analysis of variance with a significance level of 0.05, a sample size of 605 and an expected difference of 0.2 points between groups, which will provide a statistical power of at least 0.8. The 0.2 difference is the smallest reported in previous studies comparing the scores of two groups with the instruments that will be used; it was reported in the analysis of the scores of the scale of ambivalent sexism [24].

The statistical power was calculated using the software G*Power [25]. After making a slight adjustment due to the number of students currently enrolled in each school at each level, the definitive size of the experimental phase of the study will be 609 students.

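### One effectiveness objective is spread over four unranked hypotheses, at least eight constructs and two post-baseline visits, with no primary outcome, deciding time point or success rule.

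*Protocol article*

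**What the plan says.** The Objectives section of the protocol article states one main objective, the effectiveness of the program, and a secondary one on implementation. Under the main objective it hypothesizes that the intervention "i) will increase their sexuality knowledge level; (ii) will increase their preventive sexual behavior (or intentions); (iii) will favor a gender-positive attitude", with a fourth hypothesis on mental health. The four are not ranked.

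The Outcomes section follows the same layout: "The result variables of the intervention will be the following: (a) change in knowledge of sexuality", then domains (b) to (d). Six instruments measure at least eight constructs:

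- knowledge (knowledge test)
- preventive behavior or intention, self-efficacy and empowerment (all from the ad hoc survey)
- sexism (DSA)
- attitudes toward trans persons (NATP)
- modern homophobia
- psychosocial symptoms (PSC-17)

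After baseline they are measured "just after the workshop closes and 3 months after the closure", with neither visit preferred.

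The Sample size section uses "an analysis of variance with a significance level of 0.05" and does not say which outcome it serves. The difference of 0.2 was taken because it was the smallest found in previous work with the instruments; "it was reported in the analysis of the scores of the scale of ambivalent sexism".

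The Analytical methods section plans ANOVAs comparing the three evaluations, with Tukey or Games-Howell pairwise comparisons. A factorial ANOVA with evaluation as the repeated factor follows, for the variables whose main effects have been established.

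**The concern.** The trial is meant to end in one judgement: effective or not. The protocol does not say which result produces that judgement. A significant difference in knowledge alone, in sexism alone or in symptoms alone could each be put forward as support, and so could a result at either visit.

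The choice is open even within one hypothesis. Hypothesis (ii) accepts behavior or intention, and the Outcomes section lets it mean either prevention of infection and pregnancy or abstinence and postponement. The second analysis stage then follows those variables that showed an effect in the first. Tukey and Games-Howell protect the pairwise comparisons inside one ANOVA and do nothing across outcomes.

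At stake is the error rate of the main claim. Without a named outcome, visit and rule, that rate is not fixed in advance, and a reader of the results cannot tell a confirmatory finding from a selected one.

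**Working it through.** **The plan's own figures.** The protocol says: "Using a 99% confidence level and a 5% error margin, the sample framework is 605 students". With N = 6518, z = 2.58, e = 0.05 and p = 0.5, the finite-population formula N·z²·0.25 / [e²(N − 1) + z²·0.25] gives 604.05, which rounds up to 605. The number reproduces, but it is a survey-precision calculation and identifies no outcome.

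The power statement takes the test "with a significance level of 0.05, a sample size of 605 and an expected difference of 0.2 points between groups" and claims 0.8 or more for it. No SD is given. Reading 0.2 as a standardized difference with 302.5 per group, two-sided and ignoring clustering, the noncentrality is 0.2·√(302.5/2) = 2.46. Power is Φ(2.46 − 1.96) = 0.69. A one-sided test gives 0.79, and an SD of 0.87 points gives 0.81 two-sided. Under each of these readings the calculation covers one comparison on one score.

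**How many tests.** There are four hypotheses (Objectives). The eight constructs (Outcomes) are 1 knowledge + 3 ad hoc survey + 3 attitude scales + 1 PSC-17. Subscales are not counted, because no section says they will be tested separately. Visits are not multiplied in, because the analysis treats them as levels of a repeated factor.

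**Chance of at least one false positive.** Assume 0.05 two-sided per outcome, all nulls true, and each single test valid.

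- Independent tests, either direction: 1 − 0.95^k. For k = 4 this is 0.185; for k = 8 it is 0.337.
- Pairwise correlation 0.5 (assumed), either direction, equicorrelated normal statistics: 0.16 for k = 4 and 0.25 for k = 8.
- Independent tests, counting only results that favour the intervention: 1 − 0.975^k. For k = 4 this is 0.096; for k = 8 it is 0.183. The nominal figure for one test is 0.025.

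**Cost of control.** With Holm across four contrasts, the first step uses 0.05/4 = 0.0125, critical value 2.50. Power for one outcome at that step is Φ(2.46 − 2.50) = 0.48, against 0.69 at 0.05. With one primary outcome at one visit, the error rate for the claim is 0.05 and power stays at 0.69 on the same assumptions.

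**The case against.** Several points on the other side are sound.

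- The significance level of 0.05 is stated only as an input to the power calculation, so its use for every outcome test is an assumption. It is, however, the only level in the document.
- A reader might infer that a single chance positive would be declared success. The protocol does not say so. The four hypotheses are joined by *and*, so a rule that all must succeed is possible and would need no alpha adjustment. That rule is not stated either, and it would undo the power claim: at 0.69 per test, four independent tests give 0.69⁴ = 0.23 joint power, and even at 0.80 they give 0.80⁴ = 0.41.
- A reader might also multiply eight constructs by two visits and quote 16 tests with a false-positive chance of 0.37 to 0.56. The Analytical methods section does not support this. Visits are levels of one factor, pairwise comparisons within a variable are already adjusted, and no separate arm test at each visit is planned. The upper figure also requires the same scale in the same students to be independent across visits.
- The hypotheses are directional, so two-directional rates overstate the risk of a false claim of benefit.
- The multiplicity procedure, subscale handling and reporting of secondary outcomes are commonly left to a statistical analysis plan, which is not shown. Their absence is not the point here.

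What remains is that a protocol should itself name the outcome, visit and rule that decide its main objective. This article ranks its objectives and goes into detail as fine as item counts, post hoc tests and software version, yet it sets the outcomes level and adds a step that selects variables on their results.

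**Conclusion.** The point holds in a limited form. The protocol fixes one effectiveness objective and leaves undecided which outcome, time point and pattern of results would meet it. Selecting variables by observed main effect makes this worse than an omission.

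The inflation is about 0.16 to 0.19 for four tests and 0.25 to 0.34 for eight, in either direction. Restricted to results favouring the intervention, it is about 0.10 and 0.18 under independence, compared with 0.025. These figures assume 0.05 per outcome, pairwise correlations between 0 and 0.5, and individually valid tests; none of the three is given by the document. They describe what the open plan allows, not what the investigators have said they will claim.

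**What to change.** Before any arm comparison is run, amend the protocol and the registry entry to do the following.

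1. Name one deciding time point.
2. Name one pre-defined score per hypothesis as the confirmatory set. For hypothesis (ii), fix how the ad hoc survey is scored. For hypothesis (iii), use a score or composite covering sexism, trans attitudes and homophobia, or justify relying on a single scale; the DSA total alone would leave out the other two.
3. State the success rule: either one primary outcome at 0.05, or the four arm contrasts with Holm at family-wise 0.05.
4. Report every other scale, subscale and visit as secondary, with no effectiveness claim.
5. Delete the step that carries variables forward by observed main effect.

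Data collection does not change. The work is a short amendment plus the scoring decisions for hypotheses (ii) and (iii), which need thought. If Holm is chosen, first-step power falls from about 0.69 to about 0.48 at an assumed d = 0.2; clustering is ignored in both figures, and any positive within-cluster correlation would lower them. Naming one primary outcome avoids the Holm loss, at the price of leaving the other three hypotheses as supportive evidence only.
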